**Fig. 2 Fig2:**
[figure not shown]
Schedule of data collection for the HAND-1 feasibility study (Standard Protocol Items: Recommendations for Interventional Trials (SPIRIT) figure)

### Consent

Participant Information Sheets (PIS) will be provided to patients and they will have the opportunity to discuss the study before agreeing to take part. Written informed consent will be obtained from all participants. Written consent for audio-recording consultations will be obtained separately from consent for the main study. The investigator, or their nominee, and the participant or other legally authorised representative will both sign and date the Informed Consent Form.

No trial-specific procedures will be conducted before informed consent has been obtained, and participants will be reminded that they may withdraw from the trial at any time without it affecting the quality of their care in the future.

### Randomisation

Participants will be randomly allocated to treatment, in a 1:1 ratio, to treatment with either LF in an operating theatre, or NF in a clinic room, via a secure web-based system which is maintained by the Nottingham Clinical Trials Unit (NCTU) in accordance with their standard operating procedures (SOPs). Randomisation will be stratified by recruiting site and the joints affected, and will use computer-generated, permuted, balanced blocks of randomly varying size. Investigators and research nurses will access the randomisation website by means of a remote, Internet-based randomisation system developed and maintained by the NCTU. Participants will be informed orally of their treatment allocation at the point of randomisation. Participants and their GPs will also be notified of the allocation by letter.

### Blinding

Blinding of the surgeon and/or participant is not possible as it will be clear which treatment the participant receives. Photographic evidence of contracture at the 6-month follow-up will be reviewed by an assessor blind to the treatment allocation, as the participant will be asked to wear a latex glove, with the tip for the study finger cut off, which will hide any surgical scars. Trial statisticians will be blinded to treatment allocation until database lock.

### Adverse events

Both interventions in the study are widely used within current NHS practice. As such, collection of adverse events (AEs), beyond those listed as trial outcomes, is limited to recording serious adverse events (SAEs). SAEs that will be reported are death, loss of a finger and any unexpected and serious event that is potentially related to the intervention. If site staff become aware of an SAE, they will complete an SAE Report Form which will be emailed or faxed to the NCTU within 24 h, and then forwarded to the medical monitor for assessment.

### Data collection, management and analysis

Data collection, clinical assessments and taking of digital images will be carried out by trained site staff. Participant questionnaires at baseline, day of surgery, 6 weeks and 6 months will be self-completed by participants during the clinic visit. Follow-up at 2 weeks will be via postal questionnaire.

If postal follow-up questionnaires are not returned, a telephone call will be made or a reminder letter sent from the NCTU to follow up with the participant. Participants who do not receive their allocated procedure will continue to be followed up unless they opt to withdraw from the trial completely. Participants who fail to attend the clinic visit at 6 weeks will still be invited to attend at 6 months unless they opt to withdraw from trial follow-up.

Data collection and retention rates will be monitored by the Trial Management Group (TMG) throughout the trial.

### Data management and monitoring

The NCTU will undertake data management and ensure that the trial is conducted according to Good Clinical Practice (GCP) guidelines and SOPs. Data will be collected and retained in accordance with the Data Protection Act 1998. Clinic data will be either entered directly into a web-based trial database at recruiting sites, or recorded on a paper worksheet and transcribed into the database, by site users with unique login details. Participant questionnaires completed at clinic visits will be transcribed by site staff into the trial database. Postal paper questionnaires will be returned in a reply paid envelope to the NCTU for data entry into the trial database.

Data quality will be ensured by database validation checks which include missing data, out-of-range values, illogical entries and invalid responses. Data entered by sites into the trial database will be subject to monitoring and review by NCTU staff, and data queries will be raised as necessary. Detailed data management processes and procedures are documented in the HAND-1 Data Management Plan.

Monitoring of study data will be by a combination of central and on-site monitoring, in accordance with the risk-based Monitoring Plan. The chief investigator (CI) has overall responsibility for the study and is custodian of the data.

### Statistical analyses

The analysis and reporting of the trial will be in accordance with extensions of the Consolidated Standards of Reporting Trials (CONSORT) Guidelines for Pilot and Feasibility Trials [25] and Non-Pharmacologic Treatment Interventions [26].

Continuous variables will be summarised in terms of the mean, standard deviation, median, lower and upper quartiles, minimum, maximum and number of observations. Categorical variables will be summarised in terms of frequency counts and percentages. A CONSORT flow diagram showing the numbers of people approached, eligible, recruited and randomised (with reasons for exclusions) will be produced. Recruitment rates at the start and end (after modification of the recruitment method based on the qualitative studies) of the recruitment phase of the study will be compared. Numbers and characteristics of participants recruited will be summarised using appropriate descriptive statistics and compared with patients who were eligible but not randomised. Completeness of data collection will be compared between trial arms. A Statistical Analysis Plan (SAP) will be agreed before data are unblinded.

We will ‘micro-cost’ [27] NF and LF by combining resource use with unit costs provided by the hospital finance departments. Standard unit costs will be used to estimate the NHS costs of care in the 6 months post procedure [28, 29]. Descriptive summaries of NHS cost data and return to work/usual activities at each follow-up time point will be presented.

Minimum clinically important effects for each PROM will be estimated using three anchor-based responsiveness statistics: (1) standardised response mean (SRM), (2) effect size (ES) and (3) Guyatt’s Responsiveness Index (GRI). This analysis will guide the choice of PROM for use in a definitive trial of treatment of Dupuytren’s disease, along with participant ranking of the different PROMs.

Improvements in the ability to extend the finger(s) after surgery will be compared with these responsiveness indices to investigate its use as a surrogate measure of hand function and calculate its minimum clinically important difference (MCID).

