Existing studies comparing NF with LF have a number of limitations; most importantly, high risk of performance and detection biases and the use of angular measurements of finger straightness and recurrence as primary outcomes rather than a patient-reported outcome measure (PROM) or an assessment of hand function. Also, none assessed the cost of treatments to either providers or patients, and none rigorously compared the outcomes of NF with LF in each of the three subtypes of Dupuytren’s contracture. The subtype, which only affects the MCP joint (40% of all contractures), is most likely to correct successfully with NF with the least risk of damage to the digital nerves and tendons [10, 11]. Surgeons are most comfortable treating this subtype by NF [16] and it may be a specific subgroup for which NF provides equivalent or better outcomes than LF.

Although function is the main problem for patients with Dupuytren’s contracture, there is no consensus about the most appropriate PROMs to assess the outcome of treatment. Most PROMs used in hand surgery are not specific to this condition. Thirteen small studies (four retrospective and six prospective cohort and three RCTs) have used PROMs as an outcome measure for Dupuytren’s contracture [17]. They used the DASH (11 studies), the QuickDASH, Part 2 of the Patient Evaluation Measure (PEM) and the Unité Rhumatologique des Affections de la Main (URAM) (one study each). Although improvements in hand function have been recorded with all after surgery, the minimal clinically important difference (MCID) for patients with Dupuytren’s contracture has only been calculated for the URAM, which may not adequately assess loss of hand function with Dupuytren’s contracture [5].

The lack of well-designed and well-conducted trials means that the choice of treatment for Dupuytren’s contractures of the fingers mainly depends on surgeon and patient preference. A survey of 116 hand surgeons showed marked variations in treatments advised for Dupuytren’s contractures [16]. The same surgeons reported that the most important research question about surgical treatment was a comparison of NF with LF. This is also an important question for patients. A recent survey [5] of 110 patients awaiting surgery found that the most important factors in deciding which treatment to undergo were recurrence (38%), surgeon guidance (37%) and speed of recovery following surgery (25%). There is an urgent need for robust evidence to guide decision-making.

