#### Other clinical outcome measures

The following data will be collected at follow-up:Global Improvement Item [23] – self-completed by participants (to act as the anchor for the assessment of the performance of the PROMs)Complications following surgeryNHS resource use – patient-reported and obtained from medical recordsReturn to work/usual activities

The following objective outcomes will be measured at baseline and at 6-week and 6-month follow-up clinic visits:Grip strengthAngular measurement of finger straightness, with photographs taken for blinded assessment

Standardised photographs will be taken using the Nottingham Dupuytren’s Assessor which has been developed for the purposes of the study.

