### Sample size

As this is a feasibility study, a formal sample size calculation is not appropriate. It is anticipated that 50–85 participants will be recruited across the three sites. One of the primary aims of this feasibility study is to estimate response to invitation, eligibility, consent, randomisation and follow-up. Based on an expected total number to be invited of 400, estimated margins of error for these proportions will range between 5 and 13%.

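### SRM, ES and GRI measure responsiveness; as named, they do not estimate the minimum clinically important effect that the protocol assigns to them

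*Protocol article*

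**What the plan says.** Under Statistical analyses the protocol article states an aim and the means to reach it: "Minimum clinically important effects for each PROM will be estimated using three anchor-based responsiveness statistics". It names the three as SRM, ES and GRI. It then gives the use of the result: "This analysis will guide the choice of PROM for use in a definitive trial", alongside participants' own ranking of the questionnaires.

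The next paragraph extends the method to an objective measure: "Improvements in the ability to extend the finger(s) after surgery will be compared with these responsiveness indices". Its purpose is to examine finger extension as a surrogate for hand function and to calculate its MCID.

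Three other places bear on this:

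- Other clinical outcome measures lists a self-completed Global Improvement Item "to act as the anchor for the assessment of the performance of the PROMs".
- The Background says that, for patients with this condition, the MCID "has only been calculated for the URAM, which may not adequately assess loss of hand function" in Dupuytren's contracture.
- The Objectives end with calculating the sample size for a definitive study. No method is attached.

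**The concern.** The sentence pairs a target (the minimum clinically important effect of each PROM) with statistics that answer a different question. Responsiveness is how strongly a score moves relative to some measure of spread. A minimum important effect is the smallest movement that patients regard as worthwhile. A questionnaire can be highly responsive to surgery while its index says nothing about where that threshold lies.

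The label anchor-based hides the mismatch. It is not part of the definition of SRM or ES. For GRI it describes only how the stable group is found.

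The Background reports that only the URAM has an MCID in this condition and doubts that the URAM captures loss of function adequately. If the analysis is run as named, the other PROMs could leave the study with three ratios each and no threshold in scale points. Finger extension could likewise be left without a threshold in degrees.

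**Working it through.** The protocol states no MCID, effect size, power or definitive sample size, so there is no figure of its own to reproduce. The check starts from the definitions and then uses assumed values, marked as such.

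**1. Definitions**

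- SRM = mean change / SD of change. No anchor enters.
- ES = mean change / baseline SD. No anchor enters.
- GRI = minimally important change / SD of change in stable patients. The anchor picks out the stable patients. In this classical form the important change is an input, so using GRI to estimate that change is circular. Some users put the mean change in the numerator; GRI is then a responsiveness ratio like the other two.

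**2. A ratio alone does not fix a threshold in points**

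ES = 0.5 corresponds to 0.5 × 10 = 5, 0.5 × 15 = 7.5 or 0.5 × 20 = 10 points for assumed baseline SDs of 10, 15 and 20. The same holds for finger extension: comparing degrees with a unit-free index gives no number of degrees.

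**3. The indices disagree for one true MCID**

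Assume that the MCID is 0.5 baseline SD and that the SD is equal at both times. With baseline–follow-up correlation r, SD of change = √(2(1 − r)) baseline SDs. To show what the spread means, each index is also used directly as d in n per arm = 2(1.96 + 1.2816)²/d² = 21.0/d² (assumed two-sided 5%, 90% power, 1:1).

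| Index | Assumption | Value | n per arm |
|---|---|---|---|
| ES | none further | 0.50 | 85 |
| SRM | r = 0.3 | 0.5/1.183 = 0.42 | 118 |
| SRM | r = 0.5 | 0.5/1.000 = 0.50 | 85 |
| SRM | r = 0.7 | 0.5/0.775 = 0.65 | 51 |
| GRI | stable-group SD of change 0.4 | 0.5/0.4 = 1.25 | 14 |
| GRI | stable-group SD of change 0.6 | 0.5/0.6 = 0.83 | 31 |
| GRI | stable-group SD of change 0.8 | 0.5/0.8 = 0.63 | 54 |

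Stable-group SDs are in baseline SD units. The differences come only from the denominators. ES fits an unadjusted comparison of follow-up scores, and SRM a comparison of change scores. A baseline-adjusted comparison would use √(1 − r²) baseline SDs, giving 77, 64 and 43 per arm at r = 0.3, 0.5 and 0.7. The SD in GRI, taken from stable patients only, matches none of these.

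**4. When a standardised effect is a legitimate input**

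If ES is computed in the minimally improved anchor group, its numerator is an anchor-based MCID in points. An assumed MCID of 7.5 points with SD 15 gives 85 per arm, the same as ES = 0.5. So a standardised effect can feed a sample size, provided it comes from that group and uses the SD of the planned analysis.

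**5. Precision at the planned size**

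The Sample size section says: "It is anticipated that 50–85 participants will be recruited across the three sites". For a single SRM near 1 (assumed), SE ≈ √(1/n + SRM²/(2n)). The 95% half-width is 1.96 × √(0.0200 + 0.0100) = 0.34 at n = 50, and 1.96 × √(0.0118 + 0.0059) = 0.26 at n = 85. These apply to one index alone. The same patients complete all the PROMs, so a difference between two PROMs is paired and needs its own interval.

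**The case against.** The strongest defence reads the two sections together. An anchor is named, the indices are called anchor-based, and the natural meaning may be that they are computed within categories of the Global Improvement Item. The numerator in the minimally improved group would then be an MCID in points. Which category counts as minimal, and which estimator is used, are details that an analysis plan may settle, and that plan is not shown. This stands to the extent that the indices could contain an MCID. It does not remove the point. The article does not merely defer; it names both the target and the statistics. Even on this reading, three indices with different denominators are given equal standing, and the numerator, not the index, is the quantity wanted.

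A reader might also infer that these indices must be unusable for a sample size because they have no units. That is wrong, as step 4 shows.

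A reader might further infer that the definitive trial will be too small, because the average change after surgery would stand in for a minimal one. With assumed figures the gap can look large: d of 0.8 to 1.0 gives 33 to 22 per arm, against 234 to 85 for d of 0.3 to 0.5. But neither range is in the documents, and no section says that whole-cohort indices will be used or that they will set the sample size. The stated use is the choice of PROM, for which responsiveness is a proper criterion. None of the 13 objectives is MCID estimation as such; sample size is a separate objective with no stated method.

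**Conclusion.** The stated method does not serve its stated purpose, for the PROMs and for finger extension alike. This conclusion follows from the definitions and needs no assumed value. The use of the indices to compare PROMs is sound and should stay.

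The numerical spread (ES 0.50, SRM 0.42 to 0.65, GRI 0.63 to 1.25 for one MCID) illustrates that the indices are not interchangeable. It rests on the assumed correlations and stable-group SDs. An undersized main trial is a conditional risk, arising only if an index from the wrong group or on the wrong SD is carried into the sample size. Its size cannot be given from the documents. Recruitment, consent, adherence and follow-up outcomes are unaffected.

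**What to change.** Separate the two tasks in the Statistical analyses section, and in the analysis plan before unblinding:

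1. **Responsiveness.** State that SRM, ES and GRI are used only to compare responsiveness, with confidence intervals, paired for differences between PROMs. Drop the anchor-based label for SRM and ES.
2. **MCID of each PROM.** Estimate it in scale points from change by Global Improvement Item category, for example the mean change in the minimally improved group or a regression of change on the anchor. Fix in advance which category counts as minimal improvement. Report a confidence interval and the PROM–anchor correlation.
3. **Finger extension.** Do the same in degrees, in place of the comparison with the indices.
4. **Sample size.** If an MCID informs the definitive trial, use it with the observed SD that matches the planned analysis.

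The cost is a little more analysis work, as the anchor and outcomes are already collected. Intervals will be wide. Even if every participant fell in the minimally improved group, the 95% half-width for mean change would be 1.96/√50 = 0.28 to 1.96/√85 = 0.21 SDs of change. The real group will be smaller, which favours also reporting the regression on all participants. Finger extension will have fewer data at 6 months, since protocol v 2.0 allows some participants postal follow-up only.

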## Discussion

The current lack of robust evidence on treatment for Dupuytren’s contractures of the fingers means that the choice of treatment mainly depends on surgeon and patient preferences. A comparison of NF with LF has been identified as an important research question for both surgeons and patients [5]. However, it is uncertain whether surgeons will be willing to recruit, and whether patients will be willing to be randomised to such a study of two treatments which have very different patient pathways. Social circumstances, such as self-employment, duties as a carer for a relative and the financial burden of prolonged sick leave, may all influence each patient’s treatment preference, as may the desire for a straight, aesthetically satisfying finger, or to minimise the risk of needing further surgery in the future. Although some surgeons are confident with NF and willing to treat patients with well-defined cords causing either MCP or PIP joint contractures, others are reluctant to treat PIP contractures as they are concerned about damaging a digital nerve and also may not consider NF successful in treating these particular contractures. This is despite a large series reporting low incidences of digital nerve damage with NF [33] and a general acceptance that all procedures are less good at straightening PIP contractures than MCP ones. From a patient’s perspective, the options of NF and LF offer very different short- and long-term benefits, and thus many may find one treatment option suits their lifestyle much better than the other. The integrated qualitative and QRI component of the HAND-1 study will provide fundamental insights into the feasibility and design of a main trial.

The assessment of outcome of Dupuytren’s treatment with PROMs is in its infancy, and success or failure of the treatment has previously been determined by the amount of angular correction (straightening) of the flexed finger and the subsequent amount of recurrent angular deformity occurring over a pre-set time period, regardless of whether this results in the patient wishing to undergo further treatment to straighten the finger again. This is particularly unsatisfactory as the relationship between hand and finger function and joint-angle deformity is controversial.

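### Comparing finger extension with the PROMs' responsiveness indices says little about whether it can stand in for hand function; a patient-level analysis is needed

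*Protocol article*

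**What the plan says.** The Statistical analyses section of the protocol article first describes the work on the PROMs. Minimum clinically important effects are to be estimated with "three anchor-based responsiveness statistics: (1) standardised response mean (SRM), (2) effect size (ES) and (3) Guyatt’s Responsiveness Index (GRI"). The next step concerns the finger itself: improvements in extension after surgery "will be compared with these responsiveness indices to investigate its use as a surrogate measure of hand function". The same sentence gives a second purpose, the MCID of extension.

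Four other places bear on this:

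- **Objectives.** The list includes assessing how angular measurements relate to what patients report.
- **Other clinical outcome measures.** The Global Improvement Item is collected "to act as the anchor for the assessment of the performance of the PROMs". Of grip strength and the finger angle, this section says: "The following objective outcomes will be measured at baseline and at 6-week and 6-month follow-up clinic visits". The PROMs are collected at those visits too, and also at 2 weeks.
- **Discussion.** The authors write that "the relationship between hand and finger function and joint-angle deformity is controversial".
- **Limited fasciectomy.** Where an outcome needs a single finger, it is the one the patient reports before surgery as most troublesome.

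The index comparison is the only analysis the article names for the link between extension and function.

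**The concern.** A surrogate for function has to follow function from patient to patient: those who gain more extension should, on the whole, gain more function. A responsiveness index is one number per instrument for a group. It says how large the average change is against some measure of spread. Surgery is done to straighten fingers, and the Background reports that PROM scores have improved after it, so both kinds of measure can be expected to move. Similar indices would then show only that both moved.

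The stake is the advice this study gives to the definitive trial. The Background criticises earlier studies for using angle as the primary outcome, and the Discussion treats its relation to function as unsettled. An analysis that can favour angle without any patient-level association does not help to settle that.

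**Working it through.** The article gives no figure on this point, so there is none to reproduce. The check is algebra, then an illustration, then the precision of the alternative.

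**1. Formulas.** The article does not print them; the usual definitions are taken.

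- Standardised response mean (SRM) = mean change / SD of change.
- Effect size (ES) = mean change / SD at baseline.
- Guyatt's Responsiveness Index (GRI) = mean change in improved patients / SD of change in stable patients, with the groups set by the anchor.

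Pooled SRM and ES use only one instrument's own mean and SD. The covariance between angle change and PROM change appears in neither, so neither can depend on it. GRI can depend on it, but only through the anchor.

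**2. Illustration.** The documents give no mean changes, SDs or correlations, so all of these are assumptions. Changes are scaled to SD 1. Mean PROM change is 0.8 and mean angle change is 0.8 or 1.5. The anchor correlates 0.7 with PROM change, and 70% of patients count as improved. The within-patient correlation (rho) of angle change with PROM change runs from 0 to 0.9. There were 1,000,000 simulated patients per row.

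| Mean angle change | rho | SRM angle / PROM | GRI angle / PROM | Angle SRM, improved / stable |
|---|---|---|---|---|
| 0.8 | 0 | 0.80 / 0.80 | 0.80 / 1.44 | 0.80 / 0.80 |
| 0.8 | 0.3 | 0.80 / 0.80 | 0.92 / 1.44 | 0.92 / 0.57 |
| 0.8 | 0.6 | 0.80 / 0.80 | 1.08 / 1.43 | 1.06 / 0.33 |
| 0.8 | 0.9 | 0.80 / 0.80 | 1.33 / 1.44 | 1.25 / 0.08 |
| 1.5 | 0 | 1.50 / 0.80 | 1.50 / 1.43 | 1.50 / 1.50 |
| 1.5 | 0.3 | 1.50 / 0.80 | 1.63 / 1.44 | 1.62 / 1.28 |
| 1.5 | 0.6 | 1.50 / 0.80 | 1.83 / 1.44 | 1.79 / 1.09 |
| 1.5 | 0.9 | 1.50 / 0.80 | 2.16 / 1.44 | 2.03 / 0.92 |

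The table shows three things.

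- The SRM comparison does not change with rho. It agrees perfectly at rho = 0 (0.80 and 0.80) and disagrees at rho = 0.9 (1.50 and 0.80).
- GRI moves with rho but mixes it with the size of the mean change. Angle GRI is 1.50 with no association and a large mean change, against 1.33 with rho = 0.9 and a smaller one. In the first case it also slightly exceeds the PROM's 1.43.
- Splitting angle change by the anchor does carry a patient-level signal: improved and stable patients are equal at rho = 0 and well apart at rho = 0.9. That signal concerns global improvement; it reaches function only indirectly.

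**3. Precision of a patient-level analysis.** The Sample size section says: "It is anticipated that 50–85 participants will be recruited across the three sites". The Fisher interval is tanh(atanh(r) ± 1.96/√(n − 3)). For r = 0.5, atanh(r) = 0.549.

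- n = 85: half-width 1.96/√82 = 0.216, interval 0.32 to 0.64.
- n = 50: half-width 1.96/√47 = 0.286, interval 0.26 to 0.68.
- n = 40 (assumed number of pairs): half-width 1.96/√37 = 0.322, interval 0.22 to 0.70.

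These are for a simple correlation with complete pairs. A partial correlation adjusted for two baselines and three joint subtypes (two terms) replaces n − 3 with n − 7. For a partial r of 0.5, the half-widths are 1.96/√78 = 0.222, 1.96/√43 = 0.299 and 1.96/√33 = 0.341. The intervals are 0.32 to 0.65, 0.25 to 0.69 and 0.21 to 0.71. Adjustment costs little precision, though the partial correlation itself may be smaller than the simple one.

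**The case against.** The strongest reply is that the article calls the indices anchor-based. A fair reader may take it that extension will be handled in the same way, with the Global Improvement Item dividing improved from stable patients. Nothing bars this, since the item is collected from participants at follow-up. On that reading the comparison is not wholly blind to the patient-level link, and an MCID for extension can be obtained. This stands as far as it goes. A reader might infer that no anchor enters the angle analysis and that the MCID therefore cannot be calculated. The documents do not support that; they leave it unstated. Against the charitable reading, the outcomes section assigns the anchor to the PROMs, and it measures global improvement rather than hand function.

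A second reply is that the objective on angle and patient-reported outcome stands on its own, and that the full protocol or the statistical analysis plan may name a correlation or regression for it. That also stands. A reader might infer that the objective goes unanalysed, but a condensed article does not show that. The point here is narrower: a named method is given for a named purpose, and it does not suit that purpose.

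A third reply concerns weight. This is one exploratory aim among thirteen objectives of a feasibility study. The main trial's primary outcome is meant to be a PROM, chosen from the PROM indices and participants' ranking. No feasibility outcome depends on the extension analysis. This limits the severity but does not make the method suitable.

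**Conclusion.** The point holds in a limited form. For pooled SRM and ES, the lack of any dependence on within-patient correlation follows from the formulas and needs no assumption about the data. For GRI and anchor-split indices, the dependence exists but is indirect and mixed with the size of the mean change. How strong it is rests on the assumed anchor correlation of 0.7 and the 70% improved. Agreement between the indices of extension and of a PROM could therefore support surrogacy where there is no patient-level association, and disagreement could hide a strong one. The source of the MCID for extension is unclear rather than shown to be impossible.

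Severity is moderate. The sentence should be corrected, but neither the feasibility conclusions nor the choice of PROM depends on it.

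**What to change.** Replace the index comparison with a patient-level analysis on the designated study finger:

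- Regress each PROM score on the extension deficit at the same visit, adjusting for baseline PROM, baseline extension and joint subtype. Report the slope and partial correlation with 95% intervals.
- Do this at both 6 weeks and 6 months. Table 1 of the article shows that version 2.0 moved some 6-month follow-up to post only. Those participants would have no 6-month clinic measurement of angle, so the 6-week pairs are needed as well.
- State that the MCID of extension is derived from the Global Improvement Item.
- Limit the conclusion to association with function. One small trial cannot validate a surrogate for a treatment effect.

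The paired data are already in the collection schedule, so the cost is a change of wording, slightly more analysis and a more modest claim.
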